**Methods/Design:**

Forty-two public health clinics in Mexico City were randomized to treatment or control clinics. Nurses meeting eligibility criteria in treatment groups received an intensive training on screening for IPV, providing supportive referrals, and assessing for health and safety risks. Nurses meeting eligibility criteria at control clinics received the standard of care which included a one-day training focused on sensitizing staff to IPV as a health issue and referral cards to give to women. Women were screened for eligibility (currently experiencing abuse in a heterosexual relationship, 18-44 years of age, non-pregnant or in first trimester) by research assistants in private areas of waiting rooms in health clinics. Consenting women completed a baseline survey and received the study protocol for that clinic. In treatment clinics, women received the nurse delivered session at baseline and received a follow-up counseling session after three months. Surveys are conducted at baseline, three months, and fifteen months from baseline.

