## Background

Intimate partner violence (IPV) against women is a critical health, human rights, and development concern, with global estimates indicating that approximately one in three women have reported such violence at some point in their life
[1]. Research has documented a range of negative health effects from IPV, including poor mental health, unwanted pregnancies, reproductive coercion, and vulnerabilities to HIV and sexually transmitted infections
[2–7]. Within Mexico, approximately 25%-40% of women who receive health sector services have reported violence from their partners at some point in their life
[8–10]. These lifetime IPV figures are comparable to other countries in Latin America and the Caribbean
[11], and underscore the importance of interventions in health care settings. These approaches are critical as women experiencing IPV have been shown to disproportionately utilize health care services
[12], and providers may be in a unique opportunity to intervene as they are among the few outside contacts a woman may have exposure to.

Despite the potential importance of health care provider (HCP)-delivered IPV interventions and in particular, HCP IPV screening programs, such approaches remain controversial
[13, 14]. Much of the debate surrounding the screening of women for IPV by HCPs is due to mixed evidence regarding the effectiveness of such approaches in reducing IPV and improving health outcomes
[15, 16]. Moreover, IPV screening by HCPs is not universally recommended by professional health organizations
[17]. However, it remains unclear if the screening alone is an ineffective approach for addressing IPV or if HCPs do not fully adhere to screening protocols. Lack of fidelity towards consistent screening has been noted in systematic reviews due to a variety of barriers perceived by HCPs
[18]. In addition, as studies evaluating screening for IPV involve vulnerable populations of abused women, there may be high levels of attrition
[15], which may vary differentially by severity of IPV victimization and thus limit extrapolation of findings. However, the evidence-base is growing to suggest that comprehensive and systems-approaches to identifying and counseling women experiencing IPV in health settings is an effective strategy
[19–21] to address both IPV victimization and related health concerns.

Thus, rigorous evaluations, including randomized controlled trials, of these combined and integrated HCP approaches are needed

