### Intervention description

Women who participated in the study at treatment clinics received the following intervention: (1) integrated IPV and health screening; (2) supportive care; (3) safety planning and harm reduction counseling; (4) supportive referrals; and (5) booster counseling sessions at three months post baseline. The majority of materials utilized for the intervention were adapted from existing IPPF/WHR materials used in other Latin American and Caribbean contexts and were adapted to the characteristics of Mexico City
[38]. A referral directory was also created with the contact information of local community agencies that provide services to IPV victims. During the development phase of the referral directory, IPV staff at the MoH suggested that only community agencies providing free services be included. All community agencies listed in the directory were visited by research staff and addresses and phone numbers were verified. Furthermore, for each community agency, research staff obtained the name of a specific contact person to include in the referral directory. Contact names were included in the referral directory based on pilot focus group research with IPV survivors enrolled at a community agency. Pilot work revealed that women felt more comfortable asking for services if there was a specific person to contact at an agency; and that only having the name of an agency was a deterrent.

Of the agencies, two programs were highlighted: (1) SEPAVIGE, the MoH IPV program, (Gender based Violence Special Services) and UAVIF (Family Violence Prevention and Care Unit). There are approximately 14 SEPAVIGE units located primarily within hospitals. Key services include free psychological treatment and group therapy to IPV victims. UAVIF is associated with the Ministry of Social Development and it consists of 16 units in each district of Mexico City. Each unit offers legal and psychological services. They are also in charge of identifying women eligible for an IPV conditional cash transfer program. The referral directory was handed out to nurses during the training Details are presented in Table 
1.

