Nurses from all 42 health clinics were invited to participate in the training based on the following criteria: morning shift nurses (due to the walk-in basis of appointments and afternoon shifts not occurring at all clinics) and not a field nurse (due to their limited time at the health clinics). A total of 197 nurses (approximately 8% male nurses and 45% in treatment clinics) received the training. 147 nurses are actively participating in the study (49% in treatment clinics) (26% staff dropped out primarily due to staff turnover at clinics). On average, 4 nurses were trained at each health clinic. Nurses in the intervention group received a 3 day training that covered all the topics of the intervention and then nurses received up to 3 visits by research staff to practice delivering the intervention through role – playing exercises individually and in the clinics. In-depth training was needed as nurses did not feel very comfortable talking about IPV and several rounds of role playing exercises were needed for nurses to gain confidence. Role-playing exercises with research staff were chosen as it preserved rapport between nurses and the research team as well as increased confidentiality of nurses requiring additional training. All training activities were conducted by the research team, IPPF training consultants, and invited guests from local organizations and government offices who specialize in this area. Specific topics in the training included an introduction to IPV, health consequences of IPV, legal considerations in Mexico City, methods to screen for violence and assess for health implications such as reproductive coercion, safety and ethical considerations, referral methods and linkages to other organizations in the community. An educational video modeling the counseling sessions was also developed by the study team for the training of treatment nurses. This video was shown and discussed during research assistant visits to the health clinics as part of the training.

Women in the control clinics were given a referral card containing general information on IPV and a list of resources, which was consistent with the current goal for standard of care in the Mexico City MoH. The referral card is the size of a business-card so that it may easily be hidden from male partners, and is widely used in other IPV screening programs

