### Quantitative assessments & analytic plan

Our primary outcome is past-year IPV
[32] and our secondary outcomes include past-year reproductive coercion
[7, 23], use of community-based resources
[33], safety planning measures
[33], and quality of life
[34]. Descriptive statistics will be used to assess achievement of Aim 1. For the remaining aims, the follow analyses plans will be undertaken: (1) assess if randomization of health clinics was successful by examining if there are statistically significant differences between women’s demographics, by treatment arm, through chi-square or t-tests; (2) assess for differential loss to follow up by demographics and baseline IPV severity; (3) assess if IPV and secondary outcomes (reproductive coercion, safety planning, use of community resources, quality of life) differed at baseline, by treatment arm; and (4) conduct multilevel analyses of the effect of the intervention on outcomes utilizing appropriate models that will account for potential clustering for repeat measures, time, and at the clinic level. We will subsequently estimate adjusted models if any demographics significantly varied at baseline. Analyses will first be undertaken using the intent-to-treat approach. Following this, a per protocol analysis will be undertaken to determine whether effectiveness varied by adherence (i.e. attending the three month booster counseling session) and potentially nurse adherence.

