[18]. Therefore, after completing the training, all intervention nurses are visited by trained research staff. The staff member screens positive for IPV, and goes through the clinic visit, including screening, referral, and counseling following a scripted scenario. Following the health visit, the staff member completes a fidelity checklist to determine areas in which the nurse is exceeding expectations and areas in which the nurse needs improvement. All nurses are informed that they will be visited by a mock client and that all mock clients will adhere to the script used in the training. No health nurse receives more than two mock client visits throughout the study period. Feedback was given during on-site training prior to the launch of the baseline; subsequent visits were used for fidelity monitoring only. Nurses in the control group also received one visit from the mock client, but feedback will only center on standard of care, rather than comprehensive screening and counseling women. Fidelity checklists from these mock clients do not contain identifying information and were entered into a secure database upon completion. Tape recording counseling sessions were also considered as a method of assessing fidelity. However, due to safety concerns for the women, mock clients were chosen as the more appropriate method to assess intervention fidelity.

The final activity to monitor fidelity was exit interviews with women in both treatment and control clinics. Women who were participating in the study in treatment clinics were randomly selected by research staff in the clinic after they had received the intervention, based on selection of questionnaire identification numbers. Exit interviews are designed to last between 5-10 minutes where all women were asked to provide an additional written informed consent prior to completing the survey. All women in the intervention and control groups were eligible to participate in the exit interviews.

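### The per-protocol analysis defines adherence by an event only treatment-clinic women can have, with no control counterpart and no adjustment for who attends

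*Protocol article*

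**What the plan says.** All references are to the protocol article.

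- **Order of analyses (Quantitative assessments & analytic plan).** "Analyses will first be undertaken using the intent-to-treat approach". Next, "a per protocol analysis will be undertaken to determine whether effectiveness varied by adherence (i.e. attending the three month booster counseling session", with a tentative second dimension, "and potentially nurse adherence".
- **Who is offered the booster.** The abstract states: "In treatment clinics, women received the nurse delivered session at baseline and received a follow-up counseling session after three months". The Intervention description lists "booster counseling sessions at three months post baseline" as the fifth component of what women at treatment clinics receive, and Table 1 repeats it.
- **What controls receive (Intervention description, after Table 1).** "Women in the control clinics were given a referral card containing general information on IPV and a list of resources". No booster is described for them.
- **What both arms share.** Women are surveyed at baseline, three months and fifteen months, and all receive reminder calls for the two follow-up appointments (abstract; Study population, recruitment, and retention).
- **Selection by severity.** The Background says of attrition in IPV screening studies that it is something "which may vary differentially by severity of IPV victimization and thus limit extrapolation of findings".
- **Planned safeguards.** The analytic plan will check loss to follow-up against demographics and baseline IPV severity. The Discussion mentions possible adjustment for differential attrition and possible multiple imputation. Neither is tied to the adherence analysis.

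**The concern.** Attendance at three months happens after randomization and is partly the woman's own choice. If it is related to how severe the violence is, and severity predicts later violence, attenders have a different expected outcome from the arm they came from, whatever the intervention does.

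The article does not name the comparator. Two contrasts follow naturally from its wording: attenders against all controls (the usual per-protocol layout), or attenders against non-attenders within treatment clinics (a literal reading of effectiveness varying by adherence). Both mix any effect of the booster with the characteristics of women who return. At stake is interpretation. After a null intent-to-treat result, a favourable per-protocol figure could be taken as efficacy among women who completed the programme. If the selection runs the other way, a real benefit could be understated.

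**Working it through.** The plan states no figure to reproduce here, so this is a reading of the text followed by an illustration of size.

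**1. Can the criterion be applied to both arms?** The booster is described only for treatment clinics, and controls get the card. A control woman can be neither an attender nor a non-attender of the booster. The three-month appointment, by contrast, exists in both arms.

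**2. Selection effect with no treatment effect.** Let a be the share attending and g the IPV risk of non-attenders minus that of attenders. The risk in the whole arm is p = a·pA + (1 − a)·pN, with g = pN − pA. Then:

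- attenders minus all controls: pA − p = −(1 − a)·g
- attenders minus non-attenders: pA − pN = −g

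Both a and g are assumptions. The 0.55 is the complement of the article's 45% attrition allowance, used only as a low value. The article's 15% difference is read as 15 percentage points.

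| a | g = 0.10 | g = 0.20 |
|---|---|---|
| 0.55 | −0.45 × 0.10 = −4.5 points | −9.0 points |
| 0.70 | −0.30 × 0.10 = −3.0 points | −6.0 points |
| 0.85 | −0.15 × 0.10 = −1.5 points | −3.0 points |

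That is 10% to 60% of the 15-point target. If attenders carry the higher risk, every sign reverses.

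**3. A severity model.** Let severity s be standard normal, logit P(IPV) = 0.2 + 1.0·s, and logit P(attend) = 0.7 − b·s, with b = 0.25, 0.5, 0.75, 1.0 (all assumed). Attendance is then 64% to 67%. Attenders minus all women gives −1.7, −3.3, −4.8 and −6.2 points. Attenders minus non-attenders gives −5.1, −9.7, −13.8 and −17.2 points. In this model severity is the only common cause, so conditioning on it removes the bias.

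**4. Effect on a nominal 5% two-sided test, attenders against all controls.** Assume 450 women per arm, 21 clinics per arm, control IPV 50% and complete control follow-up; the article gives ICC 0.07. At a = 0.55 there are 247.5 attenders, or 11.8 per clinic. The design effect is 1 + 10.8 × 0.07 = 1.755, so the effective number is 141. For controls, 21.4 per clinic gives a design effect of 2.43 and an effective 185. With g = 0.10 the standard error is √(0.455 × 0.545/141 + 0.25/185) = 0.056, and rejection under no effect is about 13%. With g = 0.20 it is about 37%. At a = 0.70 the rates are 9% and 20%, and at a = 0.85 they are 6% and 9%.

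**5. Allowing for loss in controls.** Controls are analysed only if they return. Let control women of the attending type be retained with probability rA and the other type with rN, retention being unrelated to outcome within type. The attending-type share of analysed controls becomes a′ = a·rA / [a·rA + (1 − a)·rN], and the spurious difference is −(1 − a′)·g. Take a = 0.65, rA = 0.75, rN = 0.23 (assumed):

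- a′ = 0.4875 / (0.4875 + 0.0805) = 0.858
- at g = 0.10, the difference falls from −3.5 to −1.4 points
- at g = 0.20, it falls from −7.0 to −2.8 points
- if rN = 0, it is zero

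**The case against.** **The comparator is not stated.** A reader might infer that the plan compares selected treatment women with unselected controls. The text does not say so. It would also fit controls restricted to three-month attenders, and a condensed article may leave the comparator to a fuller plan. This stands, and the point is therefore confined to what is written: a criterion that only one arm can meet. The silence on the comparator does not rescue it, because both natural contrasts are confounded.

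**Controls are selected too.** With 45% attrition allowed for, analysed controls are also women who came back. This stands, and step 5 shows that it can reduce the bias against controls to little or nothing. It does not help the comparison with treatment-arm non-attenders.

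**The direction is assumed.** The Background says attrition may vary with severity and gives no direction; it also speaks of attrition in general, not booster attendance. This stands: the bias could go either way.

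**Intent-to-treat comes first, and severity will be examined.** The order protects the main inference. The attrition checks and possible imputation concern missing outcomes, and the article does not apply them to selection into adherence.

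**Nurse adherence.** A reader might also infer that this analysis is impossible because "Fidelity checklists from these mock clients do not contain identifying information". The documents do not support that. The statement does not rule out a clinic or study code. Nurse surveys, exit interviews and chart entries are other possible sources, and the analysis is only tentative. It is not part of this point.

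**Conclusion.** The stated criterion is a post-randomization event that can be observed in one arm only, and neither a control counterpart nor an adjustment for selection is attached to it. Followed as written, it gives an adherence estimate open to bias in either direction.

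The size cannot be known from the document. The assumed inputs put the contrast with all controls at a few percentage points, up to 9 in the most unfavourable combination tried, and less when control loss follows the same pattern. The within-arm contrast is larger under the same severity model. All these figures rest on assumed attendance, risk gap, direction and follow-up.

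The intent-to-treat result is untouched, so this is a correction to a secondary analysis, worth making before its result is interpreted.

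**What to change.** 1. Define the adherence population by attendance at the three-month visit, applied identically in both arms.
2. Weight attenders in each arm by the inverse probability of attendance given baseline IPV severity and demographics, or adjust for these variables, with clinic-level clustering in the variance.
3. Optionally, add an instrumental-variable estimate with clinic allocation as instrument and number of counselling sessions received (0, 1, 2) as exposure. State its assumptions, in particular that allocation affects outcomes only through those sessions.
4. Report the result as supportive of intent-to-treat. State that it still assumes no unmeasured predictors of attendance that also affect outcome. Note also that arm may influence attendance, and that making the visit is not identical to receiving the booster, so attendance at each should be tabulated.

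The cost is analysis-plan wording, some extra analysis and a small loss of precision. The design already schedules the three-month visit in both arms and plans to use baseline severity. By the Trial status section, baseline and three-month surveys were complete at resubmission. The fifteen-month visit is still described in the future tense, so the rule could be set before final outcomes.

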### Qualitative assessments & analytic plan

During endline data collection, research assistants will conduct 45 qualitative interviews with female participants to provide insight into observed quantitative results. In-depth interviews will consist of questions regarding perceptions of IPV, safety planning behaviors, reproductive autonomy, and quality of life. Underscoring all questions will be the woman’s perception of how, if at all, participating in the intervention created or affected these changes. Additionally, fifteen interviews were conducted with nurses at treatment clinics to understand their experiences with the HCP delivered approach between the three month follow-up period and the final endline at fifteen months. Interviews will last no longer than one hour and be conducted in Spanish. Upon transcription of audio recordings, interviews will be translated into English. All interviews will be coded using inductive thematic analysis
[45] through which emerging themes will be discussed with principal investigators.

### Process evaluation

Throughout the study period, a process evaluation is conducted, consisting of three key activities: (1) pre-post tests of the nurse training; (2) fidelity assessments with mock clients; and (3) exit interviews with women participating in the study. First, during the training of nurses, we conducted a pre-post test before and after the training to assess the change in knowledge, attitudes, and skills among nurses in regards to screening and referral for IPV. In addition to assessing nurses’ skills for addressing IPV, these pre-posttests were undertaken due to previously noted challenges that may hinder effective interventions, such as health care providers’ victim-blaming attitudes and misconceptions of IPV
[28]. Throughout the study, nurses are asked to fill out the short survey at three month intervals to assess any changes, although test-retest bias is a limitation of this process evaluation method.

Second, anonymous mock clients are used in order to assess nurses’ adherence to protocols and to serve as an opportunity to provide feedback during the training phase. Existing literature has also underscored the lack of feedback given to health care providers as a reason for infidelity to screening protocols
[18]. Therefore, after completing the training, all intervention nurses are visited by trained research staff. The staff member screens positive for IPV, and goes through the clinic visit, including screening, referral, and counseling following a scripted scenario. Following the health visit, the staff member completes a fidelity checklist to determine areas in which the nurse is exceeding expectations and areas in which the nurse needs improvement. All nurses are informed that they will be visited by a mock client and that all mock clients will adhere to the script used in the training. No health nurse receives more than two mock client visits throughout the study period. Feedback was given during on-site training prior to the launch of the baseline; subsequent visits were used for fidelity monitoring only. Nurses in the control group also received one visit from the mock client, but feedback will only center on standard of care, rather than comprehensive screening and counseling women. Fidelity checklists from these mock clients do not contain identifying information and were entered into a secure database upon completion. Tape recording counseling sessions were also considered as a method of assessing fidelity. However, due to safety concerns for the women, mock clients were chosen as the more appropriate method to assess intervention fidelity.

The final activity to monitor fidelity was exit interviews with women in both treatment and control clinics. Women who were participating in the study in treatment clinics were randomly selected by research staff in the clinic after they had received the intervention, based on selection of questionnaire identification numbers. Exit interviews are designed to last between 5-10 minutes where all women were asked to provide an additional written informed consent prior to completing the survey. All women in the intervention and control groups were eligible to participate in the exit interviews.

